### Secondary outcomes

See Table 1 for a summary of study measures (primary, secondary, exploratory) at each time-point.

#### Cognitive functioning

##### Objective cognition

Change in Global Cognition over all study time-points (up to 18 months) to determine durability of potential cognitive changes related to receiving group-based CR, or not. In addition, more specific analysis of cognitive function will involve determining changes in individual cognitive domains. Cognitive domains will include: (i) verbal learning and memory, (ii) visuospatial learning and memory, (iii) working memory, (iv) executive function, (v) sustained attention, and (vi) social cognition.

##### Subjective cognition

Self-reported cognitive functioning will be assessed using the COBRA [50], which was developed specifically for use in mood disorders. In addition, a questionnaire developed by study investigators to assess perceived cognitive performance during objective cognitive assessment will be conducted immediately following each objective cognitive assessment. Both measures will be conducted at all time-points up to, and including, 18 months.

#### General functioning

##### Objective functioning

‘Real-world’ functional competence will be assessed using the UPSA-B [58] at 6 and 12 months. This test uses role plays of everyday tasks focusing on communication skills and financial skills. Previous reports suggest that this measure is intermediate to neurocognitive abilities and actual real-world behaviour in mood disorders.

##### Subjective functioning

The FAST [55] will be used to assess self-reported general functioning. This interviewer-administered instrument has been validated in BD, and is commonly used in CR trials in mood disorders [5]. The FAST will be administered at all time-points (including 24 months) in the current study by a blind research assistant. The SAS will be used as an additional measure of social functioning, given the emphasis of IPSRT on the interpersonal domain [51], and will be completed at all time-points up to, and including, 18 months.

#### Mood symptoms

The LIFE [54] will be used to determine occurrence of episodes and sub-syndromal symptoms of MDD, hypomania or mania over the past 6 months (via telephone) at all study time-points (including 24 months). The LIFE has been extensively used in BD literature, particularly to measure number of episodes, including sub-syndromal episodes, in follow-up studies. A mean weekly score is generated based on the duration and severity of symptoms over a period of 6 months. The clinician-administered QIDS-C and YMRS will be conducted at all time-points up to, and including, 12 months to assess changes in mood symptoms over the course of the intervention period.

### Exploratory outcomes

Change in the following measures between treatment arms will be assessed as exploratory outcomes (see Table 1 for time-points of administration).Quick Inventory for Depressive Symptomatology – Self Report, QIDS-SR [52], as a measure of self-reported depression symptoms.Quality of Life in Bipolar Disorder (QoL-BD) [68]), a validated measure of quality of life for those with BD.Biological Rhythms Interview of Assessment in Neuropsychiatry (BRIAN) [69] to assess biological and sleep rhythms.Ruminative Responses Scale from the Response Style Questionnaire (RRS) [70], a measure of participants’ tendency to ruminate.Metacognitions Questionnaire – Short-form (MCQ-30 [71]) to assess individuals’ beliefs about their thinking processes.Eysenck Personality Questionnaire – Brief Version (EPQ-BV) [72] will assess individuals’ level of neuroticism and extraversion.MARS [56] will assess medication adherence in an interviewer-administered format.Biological measures: change in levels of inflammatory markers (including C-reactive protein levels (CRP) and key cytokines), androgens (Free Testosterone, Total Testosterone, Free Androgen Index, Sex Hormone Binding Globulin, Luteinizing Hormone, Follicle Stimulating Hormone Prolactin – females only), and Vitamin C will be analysed from blood samples.

#### Analysis of secondary and exploratory outcomes

To assess the effect of IPSRT-CR versus IPSRT on secondary and exploratory outcomes, general linear models will be used. These models will use treatment arm (IPSRT-CR versus IPSRT) and stratum (MDD versus BD) as fixed factors. Analyses will adopt an ITT approach.

#### Completers analysis (primary and secondary outcomes)

A sensitivity analysis will be undertaken using a completers analysis. This will include only participants who complete at least 18 IPSRT sessions, an adequate dose of CR based on number of group sessions attended and amount of computerised practice between sessions, and the relevant treatment-end assessments.

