### Development of the current trial

We have recently completed a pragmatic RCT [30] which examined a novel combination of CR, IPSRT and medication management for people with mood disorders. Individuals (*n* = 68) recently discharged from SMHS in Christchurch, New Zealand, were recruited into the trial and randomised to receive a 12-month course of IPSRT either with (IPSRT-CR) or without CR (IPSRT alone). For those randomised to IPSRT-CR, CR was incorporated into the 50-min therapy sessions from an early stage of treatment and continued for 12 sessions. However, the addition of CR to IPSRT did not significantly improve the primary outcome, Global Cognition, more than IPSRT alone. On the other hand, significantly greater improvement in psychosocial functioning and longitudinal depression symptoms was evident in the IPSRT group compared with the IPSRT-CR over the treatment period. During the trial, therapists had concerns about integrating CR into IPSRT at such an early stage of treatment. At study intake, 43% of the sample were ‘in episode’, and thus, therapists often prioritised stabilisation of mood over CR. This was a factor contributing to the comparatively low dose of CR (average of 7 h) provided in our trial compared with other recent RCTs of CR in BD [21, 22]. We therefore propose a follow-on RCT which will once again aim to optimise psychological treatment to improve cognitive function, and thereby, to improve functioning and mood outcomes in individuals with mood disorders. However, the CR component will, in this trial, be conducted at a later stage of treatment and will be delivered separately from ongoing IPSRT. For the first 6 months of the 12-month intervention period, all individuals will receive the same intervention; individual IPSRT. At 6 months, individuals will be randomised to receive additional group-based CR (8 sessions over 8 weeks) or no additional treatment. Shifting to a group approach should allow for a higher and more consistent dose of CR to be delivered, and at a point when individuals should have a more stable mood.

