### Interventions

#### Interpersonal and Social Rhythm Therapy

IPSRT combines Interpersonal Psychotherapy with a focus on social rhythms or routines in a person’s life. IPSRT will be delivered in an individual format by 8 clinicians (2 clinical psychologists, 5 mental health nurses, 1 social worker) trained in the provision of IPSRT, according to a manualised protocol. This has been adapted from the original IPSRT manual [45] by experienced IPSRT therapists (MI, MC) for patients with MDD as well as BD [29].

IPSRT will be conducted over a period of 12 months (weekly for the first 10–12 weeks, fortnightly for four months, and then monthly). Therapy frequency may increase, however, according to the patient’s mental state. A total of 24 sessions will be considered a full therapy dose, and 18 sessions as treatment completion.

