#### Analysis of primary outcome

Global Cognition will be calculated by averaging *Z*-scores across each cognitive domain, as listed above. A change *z*-score from 6- to 12-month follow-up will then be calculated using the Global Cognition score from these time-points. Change *z*-scores on Global Cognition will be compared using general linear models, with an intention-to-treat (ITT) approach. Treatment arm (IPSRT-CR versus IPSRT) and stratum (MDD versus BD) will be fixed factors, as in Douglas et al. [30].

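### The completers analysis filters on CR dose in one arm only, so it cannot test whether the intention-to-treat result is robust

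*Protocol article*

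**What the plan says.** In the section on the completers analysis, which covers primary and secondary outcomes, the protocol article states: "A sensitivity analysis will be undertaken using a completers analysis". Three conditions define the set:

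- IPSRT sessions: "This will include only participants who complete at least 18 IPSRT sessions". The IPSRT section gives the scale: "A total of 24 sessions will be considered a full therapy dose, and 18 sessions as treatment completion".
- CR dose: "an adequate dose of CR based on number of group sessions attended and amount of computerised practice between sessions".
- Assessment: "and the relevant treatment-end assessments".

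The section on development of the trial describes the two arms from month 6: "individuals will be randomised to receive additional group-based CR (8 sessions over 8 weeks) or no additional treatment". No counterpart to the CR condition is stated for controls, and no adjustment for the selection. The primary analysis is separate: change scores "will be compared using general linear models, with an intention-to-treat (ITT) approach". Under the missing-data section, an incomplete measure is given a change of zero from the previous time-point.

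**The concern.** A sensitivity analysis should vary one assumption of the main analysis and leave the rest of the comparison intact. This one changes who is compared, and does so differently in each arm. Read literally, the CR condition removes every control. Read sensibly, it removes only IPSRT-CR patients who attended or practised too little. What remains is a CR arm chosen on behaviour after randomisation, against controls who faced no such choice.

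The article itself gives reason to think that the selection is not neutral. Its account of the earlier trial says that therapists put mood stabilisation ahead of CR and that this lowered the CR dose. Dose received may therefore track clinical state.

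Agreement between this analysis and intention-to-treat could be misread as robustness, and a larger completers effect as evidence of what CR does when properly received. The analysis also drops patients without treatment-end data. A departure from the main result could thus come from the dose filter or from avoiding the zero-change rule, and the two could not be told apart.

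**Working it through.** **The plan's own figure.** The Power section gives 45 per group for an effect of 0.6 SD, two-sided α = 0.05 and 80% power. The normal approximation gives 2 × (1.960 + 0.842)² / 0.6² = 43.6, so 44. The noncentral t test gives power of 79.5% at 44 and 80.4% at 45. The figure reproduces and is not in dispute; 0.6 serves below only as a yardstick.

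**Which condition acts where.**

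| Condition | IPSRT-CR | IPSRT alone |
|---|---|---|
| At least 18 IPSRT sessions | yes | yes |
| Treatment-end assessments | yes | yes |
| Adequate CR dose | yes | cannot apply |

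**How far the 18-session rule evens this out.** The schedule is weekly for 10 to 12 weeks, then "fortnightly for four months, and then monthly". With full attendance:

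- 10 weekly sessions plus 8 fortnightly ones make 18 at week 10 + 16 = 26.
- 12 weekly sessions plus 6 fortnightly ones make 18 at week 12 + 12 = 24, and 19 by week 26.

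A full attender thus meets the rule at about the time of randomisation. Someone who misses sessions meets it later: at 75% attendance of roughly 25 sessions in the year, 0.75 × 25 ≈ 19, so only late in the year. The rule does select, but in both arms. It does not offset the CR condition.

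**Size of the shift with no true CR effect.** Let *p* be the share of the CR arm meeting the CR condition and *r* the correlation of CR engagement with cognitive change. Neither is in the documents; both are assumed. If controls were fully unselected, the shift in SD units would be r × φ(z)/p, where z cuts off the upper share p of a standard normal distribution. Rejection rates are two-sided, from the noncentral t test with 50p against 50 patients (nominal 5%).

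| p | φ(z)/p | r = 0.1 | r = 0.3 | r = −0.2 | Rejection, r = 0.1 to 0.3 |
|---|---|---|---|---|---|
| 0.9 | 0.195 | 0.02 | 0.06 | −0.04 | 5.1% to 5.9% |
| 0.7 | 0.497 | 0.05 | 0.15 | −0.10 | 5.6% to 10.3% |
| 0.5 | 0.798 | 0.08 | 0.24 | −0.16 | 6.2% to 16.1% |

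At r = 0 the shift is zero in every row.

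**With controls filtered too.** Controls must also meet the session and assessment conditions, so a simulation applied a common filter passed by 80% of both arms and then the CR condition at p = 0.7. The two kinds of engagement were correlated 0.3 or 0.7, and each correlated r with change. About 40 controls and 30 to 32 CR patients remain of 50 each.

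| r | Shift, controls | Shift, CR arm | Difference |
|---|---|---|---|
| 0.1 | 0.04 | 0.06 to 0.07 | 0.03 to 0.04 |
| 0.2 | 0.07 | 0.12 to 0.15 | 0.05 to 0.08 |
| 0.3 | 0.10 | 0.18 to 0.22 | 0.08 to 0.12 |
| −0.2 | −0.07 | −0.12 to −0.15 | −0.05 to −0.08 |

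For r = 0.1 to 0.3 the rejection rate is 5.1% to 7.6%. Against the planned effect, 0.03/0.6 = 5% and 0.12/0.6 = 20%; the extreme case with unselected controls is 0.24/0.6 = 40%.

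**The case against.** The strongest reply is that little depends on this analysis. Intention-to-treat is the stated approach for primary, secondary and exploratory outcomes, and nothing lets the completers result override it. That stands and limits the severity. It does not make the analysis a valid robustness check.

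Three stronger readings are tempting, and the documents support none of them.

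- *The analysis is biased towards CR.* No passage relates CR engagement to cognitive change. The article reports that poorer baseline performers gain more from CR, and the outcome is a change score. If abler patients attend and practise more, the filter could work against CR. Towards CR is plausible, not shown.
- *Controls are nearly unselected.* They must also reach 18 sessions, 75% of the full dose, and attend the treatment-end assessment. Without attendance figures nobody can say how few that removes. Less selected is as far as the text goes.
- *The dose cut-off is open and could be set after the results are seen.* A numeric threshold is commonly left to the analysis plan, which is not shown. Its absence from the article is no fault.

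It can also be said that completers must have treatment-end data, so this is the one stated analysis that largely avoids the zero-change rule at treatment end. That is correct, and simply deleting it would lose that check. The fix has to supply another.

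**Conclusion.** The point holds in a limited form. The CR-dose condition acts on one randomised arm, through behaviour after randomisation, so the completers comparison has lost the protection of randomisation and cannot confirm or challenge the intention-to-treat result. That follows from the text alone and needs no assumed number.

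The size and sign of the bias do need assumptions. With the common filter in both arms, moderate positive correlations give a small shift, at most about a fifth of the planned effect. The 0.24 SD case needs half the CR arm to fail the condition, r = 0.3 and controls with no selection at all, which the stated conditions contradict. Unknown direction is itself a reason not to rely on the analysis. The change is worth making, but the primary conclusion of the trial is not at risk.

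**What to change.** 1. State that the CR-dose condition applies to the IPSRT-CR arm only, and label the completers comparison descriptive and non-randomised. This costs only wording.
2. For the effect of receiving CR, use a complier-average causal effect analysis: randomised arm as instrument, all randomised patients kept and the same covariates. Define exposure by the investigators' own adequate-dose definition, counting home practice as well as attendance. Controls are not offered CR, so non-compliance is essentially one-sided and the design suits the method.
3. As a separate check on the zero-change rule, compare the arms as randomised among all patients with 6- and 12-month data, with no dose filter. This still conditions on attending the assessment, but by the same rule in both arms.

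The cost is two further models. The complier-average interval is wider: without covariates the estimate is the intention-to-treat difference divided by the qualifying share, so at an assumed 70% both estimate and interval stretch by about 1/0.70 = 1.43. The method also assumes that assignment acts only through the CR exposure as defined. Benefit from a dose below the threshold would breach that and inflate the estimate, so the limitation should be stated with the result.

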#### Missing data (primary, secondary and exploratory outcomes)

In the instance of incomplete data at any time-point from measures of primary, secondary and exploratory outcomes, a change of zero will be assumed from the previous time-point.

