### Primary outcome

The outcome measures for the trial align with ISBD Targeting Cognition Taskforce recommendations for CR trials in BD [5]. A single composite score (Global Cognition) representing overall cognitive performance at each cognitive assessment (baseline, 6 months, 12 months, 18 months) will be calculated. Change in Global Cognition from 6 months (before randomisation to group-CR) to treatment-end (12 months) will be the primary outcome measure.

Cognitive function will be assessed with a battery of cognitive tasks designed to assess verbal learning and memory, visuospatial learning and memory, sustained attention, working memory, executive functioning, psychomotor speed and social cognition. These cognitive domains are included based on recommendations from the ISBD Targeting Cognition Taskforce [5], as well as research showing these domains to be significantly impaired in acutely-unwell patients with mood disorders [6, 59] and to be sensitive to the effects of Cognitive Remediation interventions [60]. The cognitive assessment will include the following tests:Rey Auditory-Verbal Learning Task [61]Brief Visuospatial Memory Test – Revised [62]Digit Span Forwards and Backwards [63]Trail Making Test – Part A and B [64]Delis-Kaplan Executive Function System—Fluency Battery (Category Fluency, Category Switching) [64]Digit Symbol Coding [63]Continuous Performance Test [62]Stroop Task [64]Negative Affective Priming Task [65]Reading the Mind in the Eyes Test [66]Facial Expression Recognition Test [67]

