#### Power

This study is powered on the cognitive outcomes demonstrated in our preliminary RCT of Metacognitive Therapy versus Cognitive Behavioural Therapy for outpatients with MDD [16]. Metacognitive Therapy includes a simple cognitive training intervention (Attention Training Technique). A positive effect size difference between Metacognitive Therapy and Cognitive Behavioural Therapy was found on measures of visuospatial learning and attention (0.6) [16]. To detect a similar effect size for Global Cognition as statistically significant (2-tailed α = 0.05), 45 patients per group would be necessary for 80% power. We aim to recruit 50 patients per group. All statistical tests will utilise a 2-tailed *p*-value of < 0.05 to indicate statistical significance.

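### Filling every missing outcome with zero change enters invented values into the primary analysis and can bias the CR effect in either direction, depending on dropout

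*Protocol article*

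**What the plan says.** The section on missing data covers "incomplete data at any time-point from measures of primary, secondary and exploratory outcomes" with one rule: "a change of zero will be assumed from the previous time-point". This is single imputation by carrying the last value forward.

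Under Primary outcome, "Change in Global Cognition from 6 months (before randomisation to group-CR) to treatment-end (12 months) will be the primary outcome measure". Under Analysis of primary outcome, these change scores "will be compared using general linear models, with an intention-to-treat (ITT) approach", with treatment arm and diagnostic stratum as fixed factors. The same kind of model and the same missing-data rule serve the secondary and exploratory outcomes.

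On the LIFE, the Mood symptoms section says: "A mean weekly score is generated based on the duration and severity of symptoms over a period of 6 months". LIFE and FAST run to 24 months and Global Cognition to 18 months. UPSA-B is measured at 6 and 12 months only.

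The one stated sensitivity analysis is a completers analysis of the primary and secondary outcomes. It requires at least 18 IPSRT sessions, an adequate CR dose and the relevant treatment-end assessments.

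**The concern.** The endpoint is a change score, so the rule sets a leaver's endpoint directly. A missing 12-month Global Cognition score becomes an exact change of 0, which the model treats as measured. A person missing from 12 months onward also carries the 6-month value into the 18-month durability analysis.

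Zero is right only if leavers truly do not change. Some mean change between 6 and 12 months is plausible in both arms. The battery is repeated at up to four assessments, and the Discussion notes preliminary evidence that IPSRT benefits aspects of cognition. On mood, the Background cites 43% relapse within 12 months in bipolar disorder under routine care. For LIFE and FAST, the rule places an earlier value over months in which a leaver may have relapsed.

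At stake are the size of the primary estimate, the coverage of its interval and, under unequal dropout, the type I error. Within-arm worsening on mood and functioning may also go unseen.

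**Working it through.** **Inputs from the Power section.** Standardised effect 0.6, two-sided alpha 0.05, 45 per group for 80% power, 50 per group to be recruited.

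**Assumed inputs.** The article gives neither dropout rates nor a mean change in the control arm. Ranges used: 10 to 30% missing per arm, and a control change of 0, 0.3 or 0.5 SD. The SD of change is 1.

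**Plan's own figure.** A two-sample t-test needs 44.6 per group, rounded up to 45, with 80.4% power at 45. This reproduces the article. Allowing 10% loss, 45/0.9 = 50. With 50 per group and nothing missing, power is 84%.

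**Effect of the rule.** Let m be the share missing and mu the mean change (1 = CR, 0 = control). If leavers would have changed like those who stay, the expected estimate is

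(1 − m1)·mu1 − (1 − m0)·mu0.

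Rejection rates and coverage below come from simulated trials with 50 per arm, missingness unrelated to outcome and a t-test without the stratum term.

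*Equal loss, true effect 0.60.* The estimate is (1 − m) × 0.60. Power is given for control change 0 / 0.3 SD, and coverage for control change 0.

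| Loss | Estimate | Power, zero-change rule | Power, observed data | 95% interval coverage of 0.60 |
|---|---|---|---|---|
| 10% | 0.54 | 80.4 / 78.9% | 80.7 / 80.5% | 94% |
| 20% | 0.48 | 74.6 / 72.8% | 75.3 / 75.5% | 90% |
| 30% | 0.42 | 68.0 / 64.7% | 69.2 / 69.2% | 81% |

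Most of the fall from 84% comes from losing patients. The rule itself costs about 0 to 3 points at 10 to 20% loss, and about 1 to 5 points at 30%.

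*Unequal loss, true effect 0.60.*
- 30% CR, 15% control, control change 0.3: 0.70 × 0.90 − 0.85 × 0.30 = 0.630 − 0.255 = 0.375, or 0.38. Power is about 52%, against about 74% with observed data: a cost of about 22 points.
- 10% CR, 30% control, control change 0.5: 0.90 × 1.10 − 0.70 × 0.50 = 0.99 − 0.35 = 0.64, above the truth.

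*No true effect, unequal loss (30% CR, 10% control).*
- Mean change 0.5 in both arms: 0.70 × 0.50 − 0.90 × 0.50 = −0.10 SD, type I error about 9%.
- Mean change 0.3: 0.70 × 0.30 − 0.90 × 0.30 = −0.06 SD, type I error about 6%.
- Milder loss with mean change 0.3: about 5% at 15% v 10%, and 5 to 6% at 20% v 10%.
- Equal loss or zero mean change: no bias.

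*Leavers worsen by 0.5 SD, CR stayers gain 0.6, control stayers do not change.*
- 30% CR, 10% control: truth 0.70 × 0.60 − 0.30 × 0.50 + 0.10 × 0.50 = 0.32; the rule gives 0.70 × 0.60 = 0.42.
- 10% CR, 30% control: truth 0.54 − 0.05 + 0.15 = 0.64; the rule gives 0.54.
- 20% in each arm: truth 0.48 and rule 0.48. The comparison is intact, but each arm's worsening disappears.

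**The case against.** **The harm is small where the plan expects to be.** Recruiting 50 against a need of 45 leaves room for 10% loss. At that level the rule gives 0.54 and 79 to 80% power, an error of 0.06 SD towards the null. This stands. The large errors need heavier or unequal loss, for which the article gives no figures.

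**Shrinkage is conditional.** CR starts between about months 6 and 9. Someone who leaves soon after randomisation may receive none, and zero may then be closer to the truth than the mean of those who stay. This also stands. It argues for a sensitivity analysis, not for zero as the only primary assumption.

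**The design limits the problem.** Randomising at 6 months avoids early differential dropout, but losses from 6 to 24 months remain, and only one arm has extra group sessions.

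**There is a sensitivity analysis.** The completers analysis excludes missing treatment-end values, but it also selects on adherence after randomisation, with a CR-dose condition that can bind only one arm. Its result cannot show whether zero change was a fair assumption.

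**Stronger readings that the documents do not support.** A reader might infer that a missing 6-month score turns the primary outcome into a 0-to-12-month change. Envelopes are released only after the 6-month assessment, so randomised participants ordinarily have that score. A reader might also blame the rule for the whole fall in power from 84%, which under equal loss is mostly lost patients. Nor does the previous trial's less favourable mood result with CR say anything about missing data.

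**Conclusion.** The concern holds in conditional form. The article fixes a single-imputation rule for every outcome tier and applies it to an endpoint that is itself a change.

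If leavers would have changed like stayers, equal loss shrinks a true 0.60 SD in proportion: 0.54 at 10%, 0.48 at 20%. Unequal loss with a non-zero mean change moves the estimate either way (0.38 and 0.64 in the cases shown), so the rule cannot be defended as reliably conservative. Type I error reaches about 9% only with 30% v 10% loss and a 0.5 SD change in both arms, and stays near nominal in milder cases. Beyond the patients lost, the power cost is small under equal loss and about 22 points at 30% v 15%.

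For LIFE and FAST, the rule hides within-arm worsening. It distorts the arm comparison only when dropout or the amount of worsening differs by arm. A reader might infer that hidden worsening always biases the comparison; the equal-loss case shows that it does not.

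All dropout rates and mean changes are assumptions. The sample size calculation is not in question.

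**What to change.** For the primary outcome, replace zero-change imputation with a likelihood-based longitudinal model under missing-at-random. Include all randomised participants and the Global Cognition scores already scheduled at baseline, 6, 12 and 18 months. Allow no arm difference before randomisation, fit arm-by-time effects afterwards, and include stratum. The primary contrast is the arm difference at 12 months.

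Use the same approach for secondary outcomes with enough repeated measures. For UPSA-B, fit a model to its 6- and 12-month values.

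Keep zero change as a sensitivity analysis, beside one in which leavers do worse than observed patients. The second matters most for LIFE and FAST, because missing-at-random cannot recover an unobserved relapse. Describe the completers analysis as a question about adherence, not as a check on missing data.

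The cost is analysis wording and a little programming, with no new data. In the simulations, where missingness was unrelated to outcome, a simple comparison of observed data had about 5% type I error under unequal loss; without the imputed zeros, the expected difference stays at 0.60. The downside is reliance on missing-at-random. Someone lost after 6 months contributes only pre-randomisation scores, so the model avoids inventing a value but does not restore the lost information. The change should be made before outcomes are seen by arm and, if judged substantive, recorded by the route in the Protocol modification section.
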